#### Assessment timepoints

The primary outcome (MoCA) and most secondary outcomes (MMSE, MBI, HAMA, HAMD, and PSQI) will be assessed twice: at baseline and at the end of the 4-week treatment period. PSCI incidence, defined based on MoCA <26, will be assessed once at 3 months after stroke onset.

### MRI data acquisition

All MRI examinations will be performed at the MRI Center of West China Hospital, Sichuan University, on a 3.0 T scanner (Discovery MR750; GE Healthcare, Milwaukee, USA) equipped with an eight-channel phased-array head coil. Before each examination, participants will be instructed to minimize head motion, and their heads will be stabilized with foam pads. Scans will be acquired with the participant lying supine and remaining alert throughout. After acquisition, two trained neuroimaging analysts will visually inspect the magnitude and phase images for artifacts, including motion, signal dropout, and severe susceptibility distortions. Datasets with pronounced motion artifacts that preclude reliable phase unwrapping will be repeated where feasible; if repetition is not possible, the scan will be excluded from QSM analyses, and the reason will be documented.

A high-resolution structural dataset will be obtained with a three-dimensional T1-weighted spoiled gradient-echo sequence (TR/TE = 6.2/2.5 ms, field of view = 256 × 256 mm^2^, data matrix = 256 × 256, voxel size = 1.0 × 1.0 × 1.0 mm^3^). QSM will be derived from a gradient-recalled echo sequence (flip angle = 17°, field of view = 229 × 229 mm^2^, voxel size = 0.7 × 0.7 × 4.0 mm^3^, number of slices = 52, slice thickness = 4 mm).

### Clinical data analysis

Statistical analyses will be performed using IBM SPSS 26.0 (IBM, Armonk, NY, USA). The primary efficacy analyses will follow the intention-to-treat (ITT) principle (35), including all randomized participants analyzed according to their allocated group, irrespective of treatment adherence. A per-protocol (PP) population will be defined as participants who complete at least 16 of the 20 planned treatment sessions (≥80% adherence) and have the primary endpoint (week-4 MoCA) assessed. For the MRI substudy, the PP set will include participants with analyzable QSM data at both baseline and week 4.

MoCA change from baseline to week 4 will be the sole primary endpoint, and hypothesis testing for this outcome will use a two-sided significance level of 0.05. Prespecified secondary clinical outcomes (MMSE, MBI, HAMA, HAMD, PSQI, and PSCI incidence) will be analyzed without formal adjustment for multiplicity and will be interpreted as exploratory. For these endpoints, we will report effect sizes with 95% confidence intervals and regard *p*-values as descriptive, in order to avoid over-interpretation of nominal statistical significance in this pilot trial. Multiplicity for imaging analyses across QSM regions of interest will be controlled using false-discovery-rate correction as described below.

For the primary endpoint (change in MoCA from baseline to week 4), if missing data at week 4 exceeds 5% of randomized participants, multiple imputation under a missing-at-random assumption will be used as the main ITT analysis (36, 37). For secondary outcomes, analyses will primarily use available cases, and sensitivity analyses with multiple imputation may be conducted if missingness is substantial. Reasons for missing data will be documented wherever possible.

Continuous variables will be presented as mean ± standard deviation (SD) when normally distributed or median with an interquartile range (IQR) for non-normally distributed data. Between-group comparisons will utilize independent samples t-tests for normally distributed variables and Mann–Whitney U-tests otherwise. Within-group pre-post comparisons will use the Wilcoxon signed-rank test. Correlation analyses will preferentially apply Pearson’s method; if either variable violates normality, Spearman’s rank correlation will be substituted. To control for confounders, covariates including age, sex, education level, stroke severity (baseline NIHSS score), and time from stroke onset to enrolment will be incorporated into multivariable linear regression models to evaluate between-group differences in the primary endpoint and key secondary cognitive outcomes. Where available, additional vascular and imaging-related factors, such as stroke subtype, lesion side, and vascular territory, lesion volume, baseline white matter hyperintensity burden (e.g., Fazekas score), receipt of intravenous thrombolysis, and major vascular comorbidities, will be explored as candidate covariates in sensitivity analyses.

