### Sample size

This exploratory trial was primarily designed to estimate effect sizes and assess protocol feasibility. Consistent with pilot-trial recommendations for acupuncture and traditional Chinese medicine (22, 23), we set the target sample size at 30 participants per arm. Allowing for an anticipated 20% attrition, we therefore planned to enroll 36 participants in each group (total *n* = 72). For the MRI substudy, we will randomly select 15 participants per arm (*n* = 30) from the clinical cohorts, in line with Desmond and Glover’s guidance on imaging sample sizes (24). Under a two-tailed *α* = 0.05, this total sample provides approximately 80% power to detect medium-to-large correlations (r ≥ 0.50) between QSM-derived susceptibility measures and cognitive outcomes, based on Fisher’s z transformation in G*Power 3.1. Smaller associations will be interpreted with caution, and the MRI substudy is therefore primarily intended to provide preliminary estimates of effect sizes and variance components to guide the design of future, adequately powered imaging trials. With 15 participants per arm, the substudy will also have approximately 80% power to detect between-group differences in 4-week changes in regional susceptibility of approximately 0.8 standard deviations (Cohen’s d), whereas smaller treatment effects on QSM will be treated as exploratory and described descriptively.

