### Safety evaluation

Safety monitoring will focus on adverse events (AEs) related to EA, including vasovagal reactions (dizziness, nausea, pallor, transient hypotension or syncope), intolerable needling pain, local hematoma or bruising, bleeding, infection or abscess at needle sites, needle breakage, and other post-needling reactions. All AEs will be recorded on standardized case report forms, noting the onset of time, duration, severity, relationship to the intervention, actions taken, and outcome. Serious adverse events (SAEs) will be defined according to Good Clinical Practice. Participants with repeated vasovagal episodes, severe AEs, or any SAE judged related to the intervention will discontinue study treatment and may be withdrawn if further participation is unsafe. All SAEs will be reported to the principal investigator and the institutional ethics committee within 24 h and will be managed according to the Data and Safety Monitoring procedures of West China Hospital.

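### The primary analysis targets all randomised participants regardless of adherence, but the withdrawal rules may leave stoppers without a week-4 MoCA, and imputing them as missing at random may overstate the EA effect with no primary sensitivity analysis stated

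*Protocol article*

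**What the plan says.** All references are to the protocol article.

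- **Clinical data analysis, population.** The primary efficacy analysis is by intention to treat, "including all randomized participants analyzed according to their allocated group, irrespective of treatment adherence".
- **Clinical data analysis, test.** Change in MoCA from baseline to week 4 is the only primary endpoint, and "hypothesis testing for this outcome will use a two-sided significance level of 0.05".
- **Clinical data analysis, missing primary data.** The rule is conditional: "if missing data at week 4 exceeds 5% of randomized participants", then "multiple imputation under a missing-at-random assumption will be used as the main ITT analysis". Nothing is specified for 5% or less.
- **Clinical data analysis, secondary outcomes.** Available cases are used, and "sensitivity analyses with multiple imputation may be conducted if missingness is substantial". This is the only mention of a sensitivity analysis for missing data. The other sensitivity analyses in that section concern candidate covariates.
- **Withdrawal criteria.** Participants leave the trial for poor adherence, for a serious event or complication that ends the intervention, or by their own choice when they cannot finish the course.
- **Safety evaluation.** "Participants with repeated vasovagal episodes, severe AEs, or any SAE judged related to the intervention will discontinue study treatment"; withdrawal from the trial is then only a possibility, where going on would be unsafe.
- **Sample size.** "Allowing for an anticipated 20% attrition, we therefore planned to enroll 36 participants in each group".
- **Table 1 and Assessment timepoints.** MoCA is scheduled at baseline and week 4, with a further MoCA at 3 months after onset. None is scheduled between baseline and week 4.

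**The concern.** An effect that counts everyone regardless of adherence needs outcomes from people who stopped treatment, or a defensible assumption about them. The Withdrawal criteria work against the first, because stopping for several listed reasons means leaving the trial. The imputation rule supplies the second. Under missing at random, a participant without a week-4 MoCA is taken to resemble observed participants who have the same values of the variables in the model. With no MoCA between baseline and week 4, little besides arm and baseline may be available to tell stoppers from stayers. To the extent that the observed participants are those who stayed, EA stoppers are credited with the gain of EA stayers.

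If stopping early costs some of the benefit, the estimate labelled intention-to-treat is too favourable to EA. The Sample size section says that the trial exists chiefly to estimate effect sizes, so a distorted primary estimate affects its main product. As the article stands, a reader of the results would have no stated analysis of the primary endpoint showing how far the answer depends on this assumption.

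**Working it through.** **1. Inputs.** From the article: 30 per arm before attrition, 20% attrition, 36 per arm, 72 in total, trigger above 5% missing. Assumed, because the article gives no figure: the share *r* of the EA benefit kept by EA participants with missing week-4 MoCA, taken from 0 to 1. For illustration only: an effect of 2 MoCA points in those who stay, and an SD of about 3.

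**2. The plan's own figure.** 30 × 1.20 = 36 per arm and 2 × 36 = 72, so the stated numbers reproduce. Twenty per cent of 72 is 14.4 participants.

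**3. Will the trigger fire?** 5% of 72 is 3.6, so at least 4 must be missing (3/72 = 4.2%; 4/72 = 5.6%). With the number missing binomial (72, *p*), the probability of 4 or more is:

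| True missing rate *p* | P(trigger fires) |
|---|---|
| 5% | 0.49 |
| 10% | 0.94 |
| 15% | 0.997 |
| 20% | 0.9999 |

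At the planned attrition, missing-at-random imputation is in practice the main analysis.

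**4. Size of the distortion.** Let *D* be the effect in those who stay, *m* the share of the EA arm with missing week-4 MoCA, and suppose that sham stoppers do as well as sham stayers. Imputation on arm and baseline estimates *D*. The effect in all randomised participants is (1 − *m*)*D* + *m r D* = *D*[1 − *m*(1 − *r*)]. The overstatement is 1/[1 − *m*(1 − *r*)] − 1:

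| Missing in EA arm | None kept (*r* = 0) | Half kept (*r* = 0.5) | All kept (*r* = 1) |
|---|---|---|---|
| 5% | 5% | 3% | 0% |
| 10% | 11% | 5% | 0% |
| 20% | 25% | 11% | 0% |
| 30% | 43% | 18% | 0% |

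At 20% missing with none kept: 1/0.80 − 1 = 25%. With half kept: 1/0.90 − 1 = 11%.

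**5. Check by simulation.** Multiple imputation on arm and baseline, 36 per arm, 20% missing in each arm, 3,000 runs, with the illustrative effect and SD:

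| Benefit kept | Effect in all randomised | Imputed estimate |
|---|---|---|
| 0% | 1.61 | 2.02 |
| 50% | 1.80 | 2.01 |
| 100% | 1.98 | 1.99 |

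This agrees with step 4.

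**6. Direction.** If sham stoppers end *c* points below sham stayers, and a share *s* of the sham arm is missing, the all-randomised effect becomes *D*[1 − *m*(1 − *r*)] + *s c*. With *m* = *s*, imputation understates the effect once *c* exceeds *D*(1 − *r*). For *D* = 2 and *r* = 0 that means *c* above 2 points.

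**7. The 5% boundary.** With 3 of 72 missing the article specifies no imputation, so those three have no stated route into an analysis defined as covering everyone randomised. With 4 of 72 they are imputed.

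**The case against.** Multiple imputation under missing at random is a standard main analysis, and the article states the assumption openly. This is a journal article for an exploratory pilot. The imputation variables and any sensitivity analysis for the primary endpoint may sit in a statistical analysis plan that is not shown. That stands: a reader might infer that no other primary missing-data analysis is planned, but this can be said only of the article. What the article does fix is the pairing of an adherence-independent target with withdrawal of non-adherers, and the choice to mention missing-data sensitivity analysis for secondary outcomes alone.

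A reader might also infer that nearly all observed week-4 scores come from completers, so that the estimate answers what would happen if everyone finished the course. The documents do not support that. Safety evaluation lets people stop treatment without leaving the trial. The per-protocol set asks separately for 16 of 20 sessions and an observed week-4 MoCA, so participants with fewer sessions and an observed score are foreseen. Nothing is imputed for them.

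Nor do the documents show that stopping will be more frequent under EA than under sham. It is plausible given deeper, electrified needling, but no rates by arm are given, and some listed reasons for leaving are personal or social. The 20% calculation does not need unequal stopping.

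Finally, the distortion is small beside the sampling error. With about 29 observed per arm and an SD of 3, the standard error is 3 × √(2/29) = 0.79 points, and a bias of 0.2 to 0.4 points is roughly a quarter to half of that. This limits the urgency. It does not remove the point, because the confidence interval does not reflect bias from a wrong assumption about the missing scores.

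**Conclusion.** The concern holds in a limited form. The article sets a target that ignores adherence, has withdrawal rules that may leave many stoppers unmeasured at week 4, and relies on an imputation rule that would then tend to treat them like those who stayed. At 20% missing, the EA effect may be overstated by 0% to 25%, with 11% if half the benefit is kept. This rests on three assumptions: the retained share, imputation essentially on arm and baseline, and sham stoppers doing as well as sham stayers. Overstatement is possible, not certain, and the sign could reverse under step 6. Choosing missing-at-random imputation as the main analysis is not itself an error.

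The 5% trigger is a minor inconsistency with the all-randomised population. It concerns at most 3 of 72 participants and a branch that is very unlikely at the planned attrition. The change is worth making because it is cheap and protects the trial's main product, its effect estimate.

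**What to change.** 1. **Reconcile Withdrawal criteria with Clinical data analysis.** State that the week-4 MoCA already scheduled is still sought from participants who stop treatment but consent to assessment. This concerns outcome collection only, not who should stop treatment.
2. **Keep missing-at-random multiple imputation as the main analysis, without the 5% trigger,** so that any missing week-4 MoCA is imputed. Include arm, baseline MoCA, stopping status or sessions attended, and 3-month MoCA where data allow. Stopping status helps only if some stoppers have a week-4 score, and 3-month MoCA only if they are still followed.
3. **Add one prespecified sensitivity analysis for the primary endpoint,** either reference-based (EA stoppers without a week-4 score imputed from the sham arm) or delta-adjusted, and report it beside the main result. No formal pass/fail rule for robustness is needed in a pilot.

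Cost: protocol or analysis-plan wording and a few hours of analysis, with no assessment beyond those scheduled. Reference-based imputation may need software other than SPSS, and the sensitivity estimate may be less favourable than the main one.

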### Outcome measures

#### Primary outcome measurement

The primary outcome is the change in MoCA scores from baseline to the end of the 4-week treatment period. This time point corresponds to completion of the EA course and the early subacute rehabilitation phase, when treatment intensity and neuroplastic potential are highest and short-term clinical decision-making is often made. MoCA is a validated screening tool for global cognitive function, covering seven domains: visuospatial/executive function, naming, attention, language, abstraction, delayed recall, and orientation (total score = 30). Using the standardized cutoff of <26 established for cognitive impairment detection, lower scores denote greater severity of cognitive dysfunction (29). To address longer-term clinical relevance, MoCA will also be reassessed at 3 months after stroke onset, and PSCI incidence at 3 months will be analyzed as a key secondary outcome.

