### Innovation and limitations

To our knowledge, this is the first randomized trial in patients with IS-CI that integrates EA with 3.0 T QSM to quantitatively assess cerebral iron deposition as a mechanistic biomarker. Unlike previous acupuncture trials that have primarily used functional MRI, diffusion tensor imaging (DTI), or positron emission tomography (PET) to evaluate hemodynamic, connectivity, or metabolic changes, our study focuses on QSM-based iron mapping to directly probe a ferroptosis-related mechanism. However, because no molecular or biochemical markers of ferroptosis are measured, any mechanistic inferences from QSM findings will be indirect and hypothesis-generating. Methodological safeguards include concealed allocation, single-blinding of participants and outcome assessors, separation of acupuncturists, evaluators, and statisticians, and blinded data analysis. Nevertheless, practitioner blinding is not feasible, and the single-blind design carries a risk of performance bias, despite standardized training and protocolized procedures. The sham control used in this trial is also unlikely to be completely physiologically inert, as even superficial needle insertion at non-meridian, non-acupoint locations may induce non-specific sensory or segmental neuromodulatory effects. Consequently, any between-group differences are likely to represent conservative estimates of the specific effects of EA. Finally, the modest sample size and the choice of a 4-week primary endpoint, rather than 3 months, limit the ability to detect small effects and to fully characterize long-term cognitive recovery, although MoCA and PSCI incidence at 3 months are included as key secondary outcomes.

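### The main 3-month analysis uses available cases and so ignores the week-4 MoCA of anyone lost after week 4; for PSCI, two sections also give conflicting rules for participants lost to follow-up

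*Protocol article*

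**What the plan says.** The protocol article has two missing-data rules, both in Clinical data analysis. For the primary endpoint, "if missing data at week 4 exceeds 5% of randomized participants, multiple imputation under a missing-at-random assumption will be used" as the main intention-to-treat analysis. For the rest, "For secondary outcomes, analyses will primarily use available cases, and sensitivity analyses with multiple imputation may be conducted if missingness is substantial". No threshold is given for the second rule.

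The 3-month outcomes fall under the second rule. The Primary outcome measurement section says "MoCA will also be reassessed at 3 months after stroke onset, and PSCI incidence at 3 months will be analyzed as a key secondary outcome", and Innovation and limitations adds "although MoCA and PSCI incidence at 3 months are included as key secondary outcomes". Table 1 schedules MoCA at baseline, week 4 and 3 months after onset.

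The comparisons named in Clinical data analysis are a t-test or Mann–Whitney test and a multivariable linear regression. The five core covariates of the regression are age, sex, education, baseline NIHSS and time from onset. Neither baseline nor week-4 MoCA is among them, and no repeated-measures model is named.

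The PSCI incidence section defines incidence as confirmed cases over all enrolled participants.

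**The concern.** A participant who completes treatment and is then lost has two observed scores on the instrument that defines the 3-month outcomes. The week-4 score is likely to be a strong predictor of the missing one. An available-case comparison discards it and is unbiased only under a stronger assumption than the one the plan accepts for its primary endpoint. The outcomes affected are the two that the plan calls key secondary and offers as evidence of longer-term relevance.

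For PSCI the main analysis is not even determinate. An available-case rule removes lost participants. An all-enrolled denominator keeps them and treats them as non-cases. The two rules give different estimates, and neither uses what was seen at week 4.

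**Working it through.** **Inputs from the article.** There are 36 participants per arm, from a target of 30 and "Allowing for an anticipated 20% attrition". The stated figure reproduces as 30 × 1.2 = 36 (dividing instead, 30/0.8 = 37.5, would give 38). With 20% lost, 36 × 0.8 = 28.8 per arm remain. Onset is 7 to 30 days before enrolment. If treatment starts at enrolment, week 4 falls on day 35 to 58, which leaves 90 − 58 = 32 to 90 − 35 = 55 days before a 3-month visit at day 90. Loss in that interval is possible.

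**Inputs assumed.** The article gives no SD, no week-4 to 3-month correlation ρ and no split of attrition by time. I take ρ from 0.5 to 0.9 and loss after week 4 of d = 5 to 20%.

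**Standard error, mean 3-month MoCA (SD units).** On available cases, SE = √(2/(n(1 − d))) = √(2/28.8) = 0.2635 at d = 0.20. Using week-4 MoCA under missing at random multiplies this by √(1 − ρ²d):

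| ρ | SE using week-4 MoCA | reduction |
|---|---|---|
| 0.5 | 0.2569 | 2.5% |
| 0.7 | 0.2503 | 5.0% |
| 0.8 | 0.2461 | 6.6% |
| 0.9 | 0.2412 | 8.5% |

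At ρ = 0.7 the available-case SE is 2.5% too large with 10% loss and 1.2% too large with 5% loss.

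**Bias, mean 3-month MoCA.** Simulation of 6000 trials, SD 4, ρ = 0.7, 20% loss per arm, no true effect, loss logistic in week-4 MoCA with log-odds of size 1 per SD. The available-case bias is 0.49 MoCA points if the dependence is in one arm only, 0.98 if it is opposite in the two arms, and about 0 if it is the same. Regression on week-4 MoCA within arm brings all three to about 0. With a true effect of 2 points and the same mechanism in both arms, available cases gave 1.85.

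**PSCI risk difference.** Simulation of 1500 trials per setting, with:
- baseline MoCA N(20, 4) truncated below 26;
- week 4 = baseline + 2.5 + 1.5 for EA + N(0, 2.5);
- 3 months = week 4 + 0.7 + N(0, 2 or 3.5), with scores rounded and capped at 30;
- 20% lost after week 4, with logistic slope 0 or ±0.15 per week-4 MoCA point (odds ratio exp(0.75) ≈ 2.1 per 5 points);
- imputation by arm from baseline and week-4 MoCA, with 15 imputations, then the <26 cut-off.

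The true difference is about −10 to −12 percentage points. The available-case bias, in size, is:
- about 1 percentage point or less if loss depends on week-4 MoCA alike in both arms;
- about 3.5 to 4 if it does so in one arm only;
- about 6 to 7.5 if it does so in opposite directions.

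After imputation the bias is under 1 point. Monte Carlo error is about 0.12/√1500 = 0.3 points. The pooled SE that the trial would report falls by about 3 to 10%. Under random loss it goes from 0.121 to 0.113 and from 0.123 to 0.118. In the least favourable settings, with the same dependence in both arms, the fall was only 0.4 to 2%.

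**All-enrolled denominator.** If loss is random, dividing by everyone enrolled multiplies the risk difference by 1 − d, here 0.8. In the run with a 2-point true MoCA effect and low scorers lost more often in both arms, a true difference of −19.7 percentage points became −12.4.

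**The case against.** The strongest reply is that little hangs on this. The secondary outcomes are declared exploratory with descriptive p-values, the trial is a pilot, imputation is already permitted as a sensitivity analysis, and an imputation model is ordinary SAP content. That lowers the priority. It does not remove the point: the order of main and sensitivity analysis is stated in the protocol article, and a trial meant to estimate effect sizes should not leave observed data unused when it estimates them.

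Four stronger readings are tempting and are not supported.

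- *Lost participants are dropped from every secondary outcome.* For PSCI the all-enrolled denominator says otherwise. The defect there is a conflict between two sections.
- *The primary result covers 72 participants and the 3-month result about 58.* The 20% is overall attrition. The article does not place it all after week 4, and with half of it there the gains roughly halve.
- *The precision gain is well above 10%.* Even complete follow-up would lower the available-case SE by only 1 − √0.8 = 10.6%.
- *The 3-month result will be biased.* Nothing in the article suggests that loss depends on cognition differently by arm, and participants and assessors are blinded. The one-arm bias of 3.5 to 4 percentage points is about a third of an SE of 0.12.

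A further objection stands in full. By-arm imputation with two MoCA scores, five covariates and five other week-4 scores means 12 predictors on about 29 completers per arm. With 10 uninformative predictors added, the empirical SD for 3-month MoCA was 1.30 against 1.31 on available cases (change SD 3.5), so almost nothing was gained. At change SD 2 it was 1.13 against 1.20.

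**Conclusion.** The point holds at moderate size. The plan trusts missing at random for its primary result ("multiple imputation under a missing-at-random assumption will be used as the main ITT analysis") and then, for the key 3-month outcomes, makes its main analysis one that ignores observed week-4 MoCA. The cost is a standard error that could be roughly 3 to 10% lower, and exposure to a PSCI bias of 3.5 to 7.5 percentage points in scenarios where loss relates to week-4 MoCA differently by arm. If the relation is the same in both arms, the bias is about 1 point or less. These figures assume 36 per arm, all 20% lost after week 4 and the score distributions given above; they shrink with less late loss. Using week-4 MoCA removes the bias only if loss is missing at random given the observed scores.

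Separately, and without any assumption, the PSCI incidence and Clinical data analysis sections disagree about lost participants and must be reconciled.

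**What to change.** Make multiple imputation the main analysis of the 3-month outcomes. Impute the 3-month MoCA score by arm from baseline and week-4 MoCA, plus at most a few of the covariates already listed in Clinical data analysis. Apply the <26 cut-off in each completed dataset, take all randomised participants as the denominator, and pool. For 3-month MoCA itself, a repeated-measures model using baseline and week-4 scores is an equivalent choice. Keep the available-case result as the sensitivity analysis, and amend the PSCI incidence section so that a missing 3-month score is not counted as a non-case.

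Available cases may stay the main analysis for MMSE, MBI, HAMA, HAMD and PSQI at week 4, which have no measurement between baseline and that visit.

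The cost is a change of wording and slightly more analysis, with no extra patients or data. The 3-month results would rest on the missing-at-random assumption already made for the primary endpoint.

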Statistical analysis will be performed in SPSS 26.0 (IBM, Armonk, NY, USA). Within-group changes in susceptibility (post–pre) are tested with paired-samples *t*-tests, and between-group differences are assessed with independent-samples t-tests. Pearson correlation coefficients will be calculated to examine associations between changes in ROI-based susceptibility and corresponding changes in cognitive, functional, emotional, and sleep measures; if normality is violated for either variable, Spearman’s rank correlation will be used. Data normality will be assessed with the Shapiro–Wilk test. Two-sided *p*-values of < 0.05 will be considered statistically significant, and false-discovery-rate correction will be applied across the predefined ROIs to control for type I error. Given the 4-week interval and modest imaging sample size, the QSM substudy is not powered to detect small absolute susceptibility changes. We will therefore focus on within-subject changes in ROI-based susceptibility and on medium-to-large associations with cognitive outcomes, interpreting all imaging findings as exploratory.

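### Primary MoCA analysis: the plan does not say whether a normality-gated test or a regression is primary, and neither covariate list includes baseline MoCA

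*Protocol article*

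**What the plan says.** Under Primary outcome measurement: "The primary outcome is the change in MoCA scores from baseline to the end of the 4-week treatment period". Under Clinical data analysis: "MoCA change from baseline to week 4 will be the sole primary endpoint, and hypothesis testing for this outcome will use a two-sided significance level"; the level is set at 0.05.

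The same section then gives two ways of comparing the arms.

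- A general rule for continuous variables: "Between-group comparisons will utilize independent samples t-tests for normally distributed variables and Mann–Whitney U-tests otherwise".
- A regression route, namely "multivariable linear regression models to evaluate between-group differences in the primary endpoint and key secondary cognitive outcomes". Its adjustment set is given as follows: "covariates including age, sex, education level, stroke severity (baseline NIHSS score), and time from stroke onset to enrolment will be incorporated".

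A further list of vascular and imaging factors is offered as candidate covariates for sensitivity analyses. Baseline MoCA is in neither list, although Table 1 schedules it for all 72 participants. No sentence ranks the two routes.

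On missing data, once more than 5% of week-4 MoCA values are missing, "multiple imputation under a missing-at-random assumption will be used as the main ITT analysis". The Sample size section expects 20% attrition and describes the trial as aimed mainly at effect-size estimation and feasibility.

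**The concern.** MoCA is bounded at 30 and entry requires a score below 26, so a patient's change is likely to depend on the starting value through regression to the mean and the ceiling. A model that adjusts for NIHSS and education but not for the starting score ignores an obvious source of variation that is already measured in everyone. Randomisation uses a random number table with no stratification described, so a chance difference in baseline MoCA is ordinary at this size.

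The form of the main result is also left open. A t-test, a rank test and a regression could each be reported as the primary result. Which test is used depends on the observed distribution, and the rank test does not deliver what the missing-data rule and the trial's estimation aim require.

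**Working it through.** **Inputs from the protocol.** Target 30 per arm; 20% attrition; 36 enrolled per arm, 72 in total. The enrolment figure reproduces as 30 × 1.20 = 36. (Dividing by 0.80 would give 37.5, so 38.) No SD, effect size or power is stated for MoCA change, so there is no stated precision to reproduce.

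**Assumed, not in the documents.** Baseline-to-week-4 correlation ρ of 0.5 to 0.8; equal SD at both visits; no allowance for truncation or ceiling. For the five-covariate comparison, the covariates explain a share R² of 0.2 to 0.4 of baseline MoCA variance and act on week-4 MoCA only through baseline.

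**1. Against the raw change score.** In units of SD², Var(change) = 2(1 − ρ) and Var(ANCOVA) = 1 − ρ². The ratio is (1 + ρ)/2. The detectable difference at 80% power with 30 per arm is (1.96 + 0.84) × √(2/30) × the residual SD.

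| ρ | Variance ratio | Detectable difference in SD, change vs ANCOVA | n per arm for change score to match ANCOVA with 30 |
|---|---|---|---|
| 0.5 | 0.75 | 0.72 vs 0.63 | 40 |
| 0.7 | 0.85 | 0.56 vs 0.52 | 35 |
| 0.8 | 0.90 | 0.46 vs 0.43 | 33 |

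**2. Against the planned five-covariate model.** Simulation with 30 per arm and 4,000 runs per setting, adding baseline MoCA to the five covariates:

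| ρ | Variance ratio (R² 0.2; 0.4) | Further cut |
|---|---|---|
| 0.5 | 0.811; 0.858 | 14–19% |
| 0.7 | 0.903; 0.911 | 9–10% |
| 0.8 | 0.946; 0.954 | about 5% |

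**3. Chance imbalance.** The raw change score carries −(1 − ρ) of each unit of baseline difference: −0.5, −0.3 and −0.2 for the three correlations. In the simulation, the five covariates reduce this to about −0.30 to −0.41, −0.20 to −0.26 and −0.13 to −0.15. Adding baseline MoCA brings it to about 0. For scale, assume a baseline SD of 4. One standard error of the baseline difference with 36 per arm is 4 × √(2/36) = 0.94 points. The shift is then 0.94 × 0.2 to 0.94 × 0.5 = 0.19 to 0.47 points for the raw change score, and about 0.94 × 0.13 to 0.94 × 0.41 = 0.12 to 0.39 points for the five-covariate model.

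**4. Sensitivity to equal SDs.** With SDs s₀ and s₁, Var(change) − Var(ANCOVA) = (s₀ − ρs₁)². This is never negative, but it is zero when s₁ = s₀/ρ. Example: s₀ = 4, s₁ = 5, ρ = 0.8. Var(change) = 16 + 25 − 32 = 9 and Var(ANCOVA) = 25 × 0.36 = 9, so there is no gain.

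**5. Gate and imputation.** The imputation threshold is 0.05 × 72 = 3.6, so four missing values trigger it. The expected loss is 0.20 × 72 = 14.4, so imputation is the expected case. Standard pooling combines an estimate and its standard error from each imputed data set. The t-test and the regression supply these; the Mann–Whitney test as planned does not. An illustrative simulation (integer scores, entry below 26, ρ about 0.7, 29 per arm) has Shapiro–Wilk rejecting in at least one arm in about 18% of trials. A separate simulation with skewed integer data, 30 per arm and 8,000 runs gives a type I error of 4.4% for the gated procedure and 4.4% for the plain t-test.

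**The case against.** The strongest reply is that this is a condensed article of a pilot trial. The word used to introduce the covariates leaves the list open, and final model details normally belong in an analysis plan that is not shown. That has some weight. But the article does fix the tests, the gate and two detailed covariate lists, and the most obvious covariate is in neither.

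Four stronger readings are tempting, and the documents do not support them.

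- **The unadjusted test is the primary analysis.** The t-test/Mann–Whitney sentence is a general rule, and the only model tied by name to the primary endpoint is the regression. What can be said is that the two are not ranked.
- **Omitting baseline MoCA biases the result.** Under randomisation the change-score estimate is unbiased. Imbalance matters only conditionally on the baseline difference that occurs.
- **The gate inflates type I error, or imputation cannot work with this plan.** The simulated error is not raised, and imputation pools readily with the t-test and the regression. The conflict arises only if the rank test is triggered and taken as the main result. Shapiro–Wilk itself is named only in the imaging section ("Data normality will be assessed with the Shapiro–Wilk test").
- **The imaging and secondary analyses share the defect.** In the imaging section "between-group differences are assessed with independent-samples t-tests", with no rank-test alternative for that comparison, and both imaging and secondary outcomes are declared exploratory. Baseline adjustment there is optional.

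It is also fair that the 10–25% gain is measured against the weaker comparator. The five-covariate comparison gives the smaller figures.

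**Conclusion.** The point stands as one of precision and clarity; it does not threaten the trial's validity. The plan leaves the primary analysis unranked between a gated test and a regression, and in no stated version adjusts for baseline MoCA. The gain from adding it is a 10–25% variance reduction against the raw change score and about 5–19% against the planned model. Both ranges rest on equal SDs and a correlation of 0.5 to 0.8; the second also rests on the assumed role of the five covariates. The gain is modest at a correlation of 0.8 and can be near zero if week-4 scores are more spread out than baseline scores. Separately, the gate lets the data decide whether the main result is a mean difference or a rank comparison. The latter fits neither the pooled analysis nor the aim of estimating effect sizes.

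**What to change.** Name one primary analysis: a linear model (ANCOVA) of week-4 MoCA, or equivalently its change, on arm, baseline MoCA, age, sex, education, baseline NIHSS and time from onset to enrolment. When missingness exceeds 5%, fit it in each imputed data set and pool, with baseline MoCA also in the imputation model. Report the adjusted mean difference with its 95% confidence interval. Drop the normality gate for the primary endpoint and keep the rank test as a sensitivity analysis. Adjusting secondary and regional susceptibility outcomes for their own baseline values is optional.

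The cost is analysis wording only, since baseline MoCA is already collected. The model should be fixed before unblinding, and any separate analysis plan should say the same.
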